### Intervention—metacognitive therapy and work-focused module

The trial uses MCT according to the manual [31] and work-focused interventions according to the work-module that has shown promising outcomes in a previous observational study [34]. The MCT interventions and the work-focused interventions are provided in the same session by the same therapist.

#### Work-focused module

The guiding principles in the work module form a checklist to ensure that work-focus is maintained throughout the intervention. Crucially, sick leave and potential RTW is addressed from the very onset of treatment. Guiding principles are as follows:
Map the working situation, analyse job type, working conditions, relations and how symptoms affect the patient at work.Provide psychoeducation on work and mental health, including pros and cons of sick leave, e.g. risk of increased isolation and withdrawal.Map degree of sick leave and generate a gradual RTW plan. Explore the possibility of gradual RTW from the onset of therapy and communicate this to the patient’s general practitioner (GP). In the Norwegian system, GPs are responsible for sick leave, and communication with GPs is therefore an integral part of the module. Therapists are encouraged to update GPs on treatment progress, and in cooperation with patients, discuss the duration and degree of sick leave.Explore and map potential barriers for return to work, e.g. bullying, serious work conflicts, serious somatic disorder.Encourage patient to establish a dialogue with the workplace, by generating an information strategy with the patient on how to discuss their absence and symptoms in the workplace, and with whom.Explore the need for workplace adjustments. Ask the patient about possibilities to adjust the working situation for a period.

#### Metacognitive therapy

MCT is based on the Self-Regulatory Executive Function (S-REF) model which postulates how human information processing contributes to the development and maintenance of mental disorders [56, 57]. It describes how maladaptation in attentional focus and the regulation of thought processes of rumination, worry and use of maladaptive coping are derived from biassed metacognitions [44]. This maladaptive response is labelled the cognitive attentional syndrome (CAS). The CAS consists of persistent worry and rumination, threat monitoring and ineffective maladaptive coping strategies [58]. The CAS is maintained by erroneous meta-beliefs about thinking. These maladaptive metacognitions are internal information processes that control, monitor and appraise thinking. MCT indicates that there are both positive and negative metacognitive beliefs that influence information processing and choice of coping strategies. MCT states that changing these metacognitions will alleviate mental health problems. Counteracting maladaptive coping like avoidance and isolation is made explicit when drafting the initial case formulation in cooperation with the patient. The therapist uses the case formulation as a “roadmap” and reference point for the duration of the treatment, targeting metacognitions. MCT targets worry and rumination, which are cognitive processes that are also central for RTW [58, 59]. For instance, patients are less likely to RTW if they worry more about their condition, if they believe that their health issues are less treatable, less controllable, and more serious irrespective of actual severity [60, 61]. The same is true for negative expectations about work, such as believing that symptoms will worsen if one returns to work [52], in MCT terms this is considered and labelled worry. Patients often evaluate their situation more negatively than e.g. occupational physicians do [62], this may be attributable to the patients perseverative negative thinking labelled rumination in MCT. Targeting such maladaptive thinking processes and coping strategies is a central part of MCT.

The sequence in MCT treatment is as follows [38]:
Case conceptualisation, mapping symptoms and triggers.Socialise the patient to the MCT treatment model.Uncover and learn to recognise triggers for rumination or worry.Attention training, learning to shift attention in ways that are specifically designed to modify metacognitions.Challenge beliefs about uncontrollability of rumination and worry.Challenge other negative metacognitive beliefs.Challenge positive metacognitive beliefs.Eliminate maladaptive coping strategies and reinforcing new plans for regulating actions.Relapse prevention. Explore remaining worry, rumination or maladaptive coping strategies or impairments the patient may have.

The work-focused interventions in the present study are in line with the rationale and treatment protocol of MCT. It is not intended to be a stand-alone treatment programme and is linked into the case formulation of MCT whenever possible.

Anamneses contain information on work, maladaptive thought processes and maladaptive coping strategies are integrated in the MCT case formulation in line with the MCT treatment protocol. Furthermore, the emphasis is on exploring the CAS, such as worry, rumination and maladaptive coping strategies, and how these MCT constructs manifest in relation to work. Examples of maladaptive coping strategies at work may be avoidance, suppression and distraction as well as worrying prior to work tasks, rumination in hindsight or potential threat monitoring during work-related tasks.

### Treatment adherence and fidelity

Treatment is provided by a group of ten certified metacognitive therapists, educated at the MCT Institute in Manchester under the supervision of [name] and [name]. The small therapist group size facilitates treatment integrity, and all therapists are trained in work-focused interventions. All therapists participate in supervision overseen by [name], who is also the project leader. Therapists participate in weekly group supervision, monthly individual supervision and use video recordings of sessions to monitor progress. A random subset of therapy sessions will be recorded, subject to patient consent. Therapists report intervention adherence through filling out checklists at end of treatment for each patient. Adherence is also secured through written treatment logs which are part of the standard MCT protocol [38].

### Control condition and concomitant care

The control condition in the trial is a wait-list where patients receive no intervention. During the waitlist condition and the intervention, medication is administered by the participant GP in accordance with national guidelines. Use of medication and health services are recorded at assessment, start of treatment and end of treatment through self-report forms. No other psychotherapy will be allowed during the 12-week treatment period of the trial. However, the frequency of accessing additional therapy during the follow-up period will be assessed. Somatic health status, including any somatic diagnoses, is recorded by self-report and will be reported as part of patient characteristics in all publications.

### Safety reporting

No adverse consequences are expected. However, in the event of any adverse effect, patients will be treated in accordance with national health care guidelines to ensure optimal care. Any patient can discontinue participation in the trial at any time without disclosing their reasons. Any adverse events will be recorded and reported in accordance with Good Clinical Practice and national patient safety regulations. The clinic in which the study is taking place is part of the national health service, and the study is subject to all rules and regulations that regulate specialised health care, including mandatory reporting of adverse events.

The study will be monitored by a trial research committee and an international advisory board. Both are involved in overseeing the trial and assuring that research ethics and principals for good research are followed.

### Retention and follow-up

We will strive to collect data on all patients, regardless of whether they complete treatment or not. The clinic has collected self-report questionnaires from patients for clinical use since its inception in 2007, and the infrastructure for data collection is well-established. For the post-treatment follow-up at 6, and 12 months, self-report measures will be mailed to the patient. Patients will also receive a reminder per SMS and a follow-up phone call. Data on sick leave will be collected from national registries and is thus less vulnerable to loss to follow-up.

### Sample size estimate

Sick leave will be operationalised as a percentage of sick leave collected both from the national registry and self-report. To evaluate the intervention versus wait-list condition, the percentage of sick leave status of the intervention group will be compared at end of treatment to the status of the control group at the end of the waiting period. The minimum expected effect is that of the treatment reported in the naturalistic follow-up study at the same clinic [56]. Data from this study showed a self-reported full RTW response rate of 0.41 in the intervention group versus 0.26 in the wait-list control group, with a pooled standard deviation of 0.4 [34]. Given this result, to detect differences in a dichotomous outcome variable we would need approximately 120 in each treatment group to have an 80% chance of detecting a significant difference at a two-sided significance level of 0.05 [63]. For the anxiety and depressive symptoms, detecting a 5 point difference between intervention and waitlist control group using a pooled standard deviation of 6.95, we need approximately 31 participants in each of the group in order to have an 80% chance of detecting a significant difference at a two-sided significance level of 0.05 [28, 64].

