In addition to the need for more rigorous studies, there is also room for improving treatment outcomes [22]. The majority of the work-focused treatment studies have been modelled on CBT as the evidence for its efficacy in treating depression and anxiety symptoms is well explored [11]. The research in general shows significant improvement in symptoms in approximately 50% of patients but this masks considerable variability in outcomes across studies [23, 24]. Furthermore, a treatment where half of the patients do not get significantly better leaves considerable room for improvement. Follow-up of 1- and 2-year relapse rates show that 25–50% of patients treated for depression relapse, and the corresponding number for anxiety is about 15% [25, 26]. In recent years, metacognitive therapy (MCT) has shown excellent results in treating depression and anxiety [27]. Recent studies on MCT in Norway have shown recovery rates of 65% and 70% for anxiety and depression, with similar rates at 1 and 3-year follow-up [28–31]. In Denmark a comparison of MCT with CBT for depression showed that MCT was superior, achieving a 74% recovery rate compared with 52% in CBT [32]. A separate Norwegian study also showed that metacognitions, a central construct in MCT, may also predict work status [33]. This indicates that MCT is a very promising treatment which may represent a significant step forward in terms of recovery from depression and anxiety and may be more effective than existing approaches.

An observational study at Diakonhjemmet Hospital in Norway, which included work-focus interventions found that significantly more patients returned fully to work at end of treatment in the intervention group than in the wait-list group (41.4% versus 26.3%) [34]. The findings from this study are promising, warranting further exploration in a RCT.

To date, no study has investigated Metacognitive therapy (MCT) and work-focused interventions together. This waitlist RCT primarily evaluates the changes in symptoms of depression and anxiety, and percentage of sick leave, and secondarily whether the treatment is cost-effective. The main hypotheses to be tested are:

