### Randomisation and blinding

After the initial screening session, eligible patients will be randomised using WebCRF, a web-based program provided by the Unit for Applied Clinical Research at the Norwegian University of Science and Technology (NTNU). The block randomisation is stratified on gender and degree of sick leave. The study will include 240 patients in all. Half of the patients will be allocated to the treatment condition (*n* = 120) and the other half to the wait-list conditions (*n* = 120). Half of the patients in the wait-list condition wait 8 weeks, the other half wait 12 weeks before commencing treatment. Because the treatment is offered in an ordinary outpatient clinic, the duration of the treatment will vary. To control for potential differences in treatment duration the wait-list condition also contained two different conditions.

Guidelines from the Norwegian Directorate for Health and Social Affairs state that patients who fulfil the criteria for a moderate depressive episode according to ICD-10 have the right to specialised health care within 8 weeks of referral [45, 46]. Thus, patients with this diagnosis will be allocated evenly between the treatment condition and the 8-week waiting condition. No patients with moderate depressive episode will be allocated to the 12-week waiting condition due to Norwegian law.

The randomisation procedure is performed by administrative personnel who otherwise are not involved in the patient’s treatment. Clinicians are not involved in the randomisation procedure. The initial assessment session is carried out by a different therapist than the one the patient sees for treatment. Blinding the treatment therapist to group allocation is not doable for logistical reasons (e.g. date of journal documents). Assessment of diagnosis at end of treatment using the Mini-International Diagnostic Interview is carried out by an independent clinician who has no prior contact with the patient.

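### At 120 per group, power for full return to work of 41% versus 26% is about 70%, not the stated 80%, and the quoted standard deviation of 0.4 does not fit those rates

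*Protocol article*

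**What the plan says.** Under Sample size estimate, the article takes its expected effect from an earlier study at the same clinic: a "self-reported full RTW response rate of 0.41 in the intervention group versus 0.26 in the wait-list control group". The same sentence reports these rates as coming "with a pooled standard deviation of 0.4". The Background gives the rates to one decimal, "41.4% versus 26.3" percent. From this the article concludes that, "to detect differences in a dichotomous outcome variable we would need approximately 120 in each treatment group to have an 80% chance", taking a two-sided level of 0.05. No formula is named.

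Randomisation and blinding fixes the total and splits it equally: "The study will include 240 patients in all". The separate calculation for symptoms needs only about 31 per group, so the total of 240 rests on return to work.

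Two other statements bear on how far the point reaches. Sample size estimate defines sick leave as a percentage, taken from both the registry and self-report. Data analysis and data management calls the primary outcomes continuous and assigns them to a linear mixed model.

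**The concern.** For a yes/no outcome, the two rates, the significance level and the group size determine the power, apart from small differences between formulas. The article states all of these, so its 80% can be checked directly, and it looks too high for a 15-point difference with 120 per group. The standard deviation is a second warning sign: a yes/no variable has its standard deviation fixed by its rate, and 0.4 is too small for rates of 0.41 and 0.26.

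At stake is how the return-to-work result is read. If the trial report repeats 80% and full return to work shows no significant difference, readers will assume a 20% chance of missing the expected effect. For that comparison the chance is about 30%.

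**Working it through.** **Inputs.** Rates 0.41 and 0.26, two-sided 0.05, power 80%, about 120 per group (Sample size estimate); 41.4% and 26.3% (Background); equal allocation, 240 in total (Randomisation and blinding). Normal quantiles are 1.960 and 0.842, and (1.960 + 0.842)² = 7.849.

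**Can the stated 120 be reproduced?**

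- Means formula with the quoted standard deviation: n = 2 × 7.849 × 0.4² / 0.15² = 111.6, so 112 per group (113 with the t distribution). Power at 120 is 82.8% (82.5% with the t distribution). This is near 120 but does not give it; a standard deviation of about 0.414 would be needed.
- Two proportions, one-sided 5%: the unpooled formula gives 6.183 × 0.4343 / 0.0225 = 119.3, and the pooled formula gives 121.4 (122 after rounding up). Power at 120 is 79.6% to 80.2%. This matches, but the article says two-sided.
- Two proportions, two-sided 5%, as stated: not reproduced, as shown next.

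**Two-sided sample size for 80% power.**

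- Sum of the two variances: 0.41 × 0.59 + 0.26 × 0.74 = 0.2419 + 0.1924 = 0.4343.
- Unpooled: n = 7.849 × 0.4343 / 0.15² = 151.5, so 152 per group.
- Pooled under the null: the mean rate is 0.335 and 2 × 0.335 × 0.665 = 0.44555. Then n = [(1.960 × √0.44555 + 0.842 × √0.4343) / 0.15]² = 154.2, so 155 per group.
- With a continuity correction: 168 per group.
- With 0.414 and 0.263: 151 (unpooled) or 153 (pooled) per group.

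**Two-sided power at 120 per group.**

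- Pooled: (0.15 × √120 − 1.960 × √0.44555) / √0.4343 = (1.643 − 1.308) / 0.659 = 0.508, and Φ(0.508) = 69.4%.
- Other methods for 0.41 versus 0.26: unpooled 70.3%, arcsine 69.7%, exact enumeration of the chi-square test 69.5%, continuity-corrected about 64%.
- With 0.414 and 0.263: 69.8% (exact 69.9%).
- Effect detectable with about 80% power: 43% versus 26% gives 79.5% (pooled) to 80.4% (unpooled).

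**The standard deviation.** √(0.41 × 0.59) = 0.492 and √(0.26 × 0.74) = 0.439. Pooled with equal groups: √(0.4343 / 2) = 0.466; taken at the mean rate: √(0.335 × 0.665) = 0.472. A pooled within-group value must lie between the two arms' values, and 0.4 is below both. It would fit a rate of 0.20, since 0.20 × 0.80 = 0.16 = 0.4².

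**The case against.** The strongest objection is that full return to work is not the form in which the primary outcome is analysed. Sick leave is defined as a percentage and the primary outcomes go into a linear mixed model with repeated measures, so 70% is not the power of the planned primary analysis. This stands and limits the point. The power of that model could be higher or lower, and the article lacks the variances and correlations needed to compute it. The objection does not rescue the stated 80%, which the article itself gives for a dichotomous outcome and uses to justify 120 per group.

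A reader might infer that the error came from putting 0.4 into a formula for means. The article does not support that: it names no formula, that route gives 112 rather than 120, and a one-sided 5% test of proportions fits better at 119 to 122. Nothing confirms the one-sided route either. Nor is 0.4 impossible for every yes/no outcome. It is incompatible with the rates printed beside it, and the article attributes it to an earlier study that is not available here, so it may describe another quantity.

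A reader might also take the lack of any allowance for loss as a further drop in power. Losses of 10%, 15% or 20% would give about 65%, 62% or 60% in a complete-case comparison, but those rates are assumptions. Retention and follow-up notes that registry sick-leave data are less vulnerable to loss, so these figures are illustrative only and form no part of the error.

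**Conclusion.** The power statement is wrong as written. For full return to work of 41% versus 26%, a two-sided 5% test and 120 per group, power is about 70%, roughly 10 percentage points below the claim. Reaching 80% would take 32 to 35 more patients per group (152 to 155 in place of 120). The gap is too large for the word approximately to cover, and it appears with every standard two-sided method tried. Separately, the quoted standard deviation of 0.4 contradicts the quoted rates.

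The conclusion rests only on the article's own rates, significance level and group size, with complete data. It does not depend on how 120 was obtained, which cannot be determined. The miss risk of about 30% belongs to the dichotomous comparison alone and should not be carried over to the mixed model of sick-leave percentage.

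**What to change.** Replace the power sentence for return to work with wording such as: *120 per group gives about 70% power (two-sided 0.05) for full return to work of 41% versus 26%; 80% power is reached at about 43% versus 26%.* Remove the pooled standard deviation of 0.4, or explain what it measures and reconcile it with the rates. Add one sentence saying that this power refers to the dichotomous comparison of full return to work and not to the linear mixed model of sick-leave percentage.

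Trial status reports that recruitment finished in May 2021, so this is a change of wording only. It needs no extra patients and alters no planned analysis. The cost is a less favourable stated power, which the trial report should carry in place of 80%.

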### Data analysis and data management

Data analysis will be conducted in accordance with a pre-specified data-analysis plan. All data will be analysed based on an intention-to-treat (ITT) approach, and analyses will include all randomised patients. The primary outcomes are continuous measures in a repeated design, therefore linear mixed-model analysis (LMM) will be run. For effects on depression and anxiety, reliable clinical change index and Cohen’s *d* for effect size will be reported, the difference between groups will be analysed using mixed model ANOVA.

All data is recorded and managed in accordance with national health service guidelines. Access to data is managed by Diakonhjemmet Hospital.

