## Methods

### Primary objectives

The primary objective of the study is to examine the impact of MCT plus work-focus interventions on symptoms of depression and anxiety and percentage of sick leave at end of treatment. Other measurement points will be included in secondary objectives. Self-report data will be collected at initial assessment, start and end of treatment as well as at 6 and 12 months follow-up. Data from the national registry related to percentage of sick leave is collected up to 24 months prior to and 48 months after treatment. A schematic overview of measurements and endpoints are included in Fig. 2. The following measures will be used:
Changes in the degree of sick leave recorded from National registries (time frame: from 2 years prior to intervention to 4 years after intervention).Changes in the degree of sick leave from patient self-report (time frame: from pre-treatment, to post-treatment (12 weeks), and at 6 months and at 1 year follow-up).Changes in anxiety symptoms as recorded by Beck Anxiety Inventory (BAI) [35] (time frame: from pre-treatment to post-treatment (12 weeks) and at 6 months and 1 year follow-up).Changes in depressive symptoms measured by Beck Depression Inventory II (BDI-II) [36] (time frame: from pre-treatment to post-treatment (12 weeks) and at 6 months and 1 year follow-up).

BDI-II and BAI are self-reported measures. For the percentage of sick leave, both national registry data will be collected from the National Labour and Welfare administration in addition to self-report.

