### Study design

The study is an RCT comparing MCT and work-focused interventions given immediately after screening (< 1 week after assessment) with a wait-list condition. We chose a waitlist design as a “no treatment” control group is not feasible due to ethical reasons, and comparison with another active treatment was not feasible due to practical reasons. The intervention will be given as manualised treatment based on diagnostic-specific MCT as specified in the manual from 2009 by Wells [44]. Work-focused interventions will be based on the work module used in Lagerveld’s study but adjusted for a Norwegian context and MCT [18].

A summary flowchart of the procedure is found in Fig. 1. Treatment duration is up to weekly 12 sessions, but as the study takes place in a national health service outpatient clinic, the number of sessions may vary. The treatment primary outcome is measured at end of treatment or session 12 if treatment duration is longer, whichever comes first. In all, 240 patients who are on sick leave due to anxiety or depression at the time of enrolment will be recruited. The study uses a block randomisation with a stratification based on gender and degree of sick leave to ensure an equal balance of gender and sick leave across the conditions. Degree of sick leave indicates the percentage of ordinary working hours. Someone working half their normal number of hours would thus be on 50% sick leave. An equal number of patients are randomised to the treatment and wait-list condition. The waitlist condition group is subdivided into two equal groups that wait either 8 or 12 weeks before treatment, because in the sample there will be variation in the duration of the treatment intervention. The registry data will benchmark the current study against previous studies that have used CBT with regards to RTW. The maximum waiting time of 12 weeks is identical to the average waiting time at the clinic, to ensure that participation in the study does not delay treatment for patients. The reason for differentiating the waitlist condition is twofold. First, Norwegian law dictates that patients with moderate to severe depressive episodes should not wait longer than 8 weeks. Secondly, it is important to investigate if the duration of waiting in itself accounts for differences in change, e.g. whether shorter or longer waiting times improves outcomes.

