##### Sick leave

Self-reported percentage of sick leave will be collected pre- and post-treatment as well as 6 and 12 months follow-up. In addition, the study has permission to collect data from national register data on the percentage of sick leave up to 24 months prior to treatment and 48 months after treatment. Norway has extensive national registries for sick leave and benefit pay-outs, creating a unique opportunity to evaluate treatment effects in this regard. The 2 years prior to treatment will serve to establish a baseline. Figure 2 shows the schedule for the collection of self-report measures.

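### Neither the sick-leave comparison nor the symptom analysis names the screening value or the stratification factors as model terms; adjusting for them would cost nothing and could add precision, above all for sick leave

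*Protocol article*

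**What the plan says.** Three descriptions of the co-primary comparisons stand in the protocol article.

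- **Sample size estimate**, on sick leave: "the percentage of sick leave status of the intervention group will be compared at end of treatment to the status of the control group", the control status being taken at the end of the waiting period.
- **Data analysis and data management**, on the primary outcomes together: "The primary outcomes are continuous measures in a repeated design, therefore linear mixed-model analysis (LMM) will be run".
- The same section, on depression and anxiety only: "the difference between groups will be analysed using mixed model ANOVA".

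That section also places the detail elsewhere: "Data analysis will be conducted in accordance with a pre-specified data-analysis plan". That plan is not shown.

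On the design side, Study design says "The study uses a block randomisation with a stratification based on gender and degree of sick leave", and Randomisation and blinding repeats the two factors. Primary objectives lists self-report data at initial assessment, and Recruitment process and context has questionnaires mailed before the screening session, so before randomisation. The Sick leave section adds "Self-reported percentage of sick leave will be collected pre- and post-treatment as well as 6 and 12 months follow-up", and says of the registry data: "The 2 years prior to treatment will serve to establish a baseline".

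No sentence lists the fixed effects of any model.

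**The concern.** Degree of sick leave is both a randomisation stratum and the baseline value of a co-primary outcome. It is likely to predict the outcome, and it is already recorded. A comparison of end status does not use it. A mixed ANOVA with one reading before and one after uses it only by subtraction, because its group-by-time test is the t-test on change scores. Stratifying on a prognostic factor and then leaving it out of the model generally makes the standard errors too large, so the balance obtained by design is not turned into precision.

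Sick leave is where this matters. It drives the sample size of 240, whereas the symptom scales need only about 31 per group. Recruitment is complete (Trial status), so the analysis is the main remaining place to gain precision.

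The choice of baseline also needs stating. Primary objectives words the outcomes as change from pre-treatment. For wait-list patients the start of treatment comes after the control period, so the randomised comparison needs the screening value.

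**Working it through.** **Inputs.** From Sample size estimate: full return to work 0.41 v 0.26 (difference 0.15), SD 0.4, about 120 per group, 80% power, two-sided 0.05; for symptoms, 5 points with SD 6.95 and about 31 per group. The article gives no correlation between baseline and outcome, so rho = 0.5 is an assumption, shown with the range 0.3 to 0.7. It gives no effect size for percentage sick leave either, so the 0.15 difference is borrowed from the dichotomous outcome.

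**The plan's own figures.** For symptoms, n = 2(1.96 + 0.842)² × 6.95² / 5² gives 31 per group, as stated. For sick leave, the same formula with 0.15 and SD 0.4 gives 112. Treating 0.41 v 0.26 as two proportions gives 155. The stated 120 follows from neither. That is a separate matter, but it is why two starting powers are carried below:

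- SD 0.4: 0.15 / (0.4 × √(2/120)) = 2.905, and Φ(2.905 − 1.96) = 82.8%.
- Two proportions: 69.4% at 120 per group. The SD implied by the two rates is √((0.41×0.59 + 0.26×0.74)/2) = 0.466, not 0.4.

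**Variance of the arm comparison, relative to post-only.**

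- Post-only: 1
- Change score, or unconstrained group-by-time with one value before and one after: 2(1 − rho)
- ANCOVA, or a mixed model with a common baseline mean: 1 − rho²

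For 0 < rho < 1 the third is below both others, since 1 − rho² < 1 and 1 − rho² = (1 − rho)(1 + rho) < 2(1 − rho).

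**Power for sick leave** = Φ(signal / √factor − 1.96), 120 per group. At rho = 0.5 with SD 0.4, 2.905 / √0.75 = 3.354, and Φ(3.354 − 1.96) = 91.8%.

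| rho | Factors: change, adjusted | SD 0.4: post / change / adjusted | Two proportions: post / change / adjusted |
|---|---|---|---|
| 0.3 | 1.40, 0.91 | 82.8 / 69.0 / 86.1% | 69.4 / 55.0 / 73.5% |
| 0.5 | 1.00, 0.75 | 82.8 / 82.8 / 91.8% | 69.4 / 69.4 / 81.3% |
| 0.7 | 0.60, 0.51 | 82.8 / 96.3 / 98.2% | 69.4 / 89.0 / 93.3% |

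Gains before rounding:

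- At rho = 0.5: +9.1 points (SD 0.4) and +11.9 points (two proportions), over either unadjusted analysis.
- At rho = 0.3: +3.3 to +4.0 over post-only and +17.1 to +18.5 over change score.
- At rho = 0.7: +15.5 to +23.8 over post-only and +1.9 to +4.3 over change score.
- Over a mixed model with a common baseline mean: about 0 at any rho.

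A simulation with a standardised difference of 0.375 (0.15/0.4), 120 per group and rho = 0.5 gave 82.4% (post-only), 82.1% (change score) and 90.9% (ANCOVA).

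**Symptoms.** With a standardised difference of 5/6.95 = 0.719 and 120 per group, power is already 99.98%. The interval width of the adjusted analysis relative to change score is √((1 − rho²)/(2(1 − rho))) = √((1 + rho)/2): 0.806 at rho = 0.3 and 0.922 at rho = 0.7, so about 19% to 8% narrower.

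**The case against.** A reader might infer that the trial's analysis adjusts for neither baseline sick leave nor the strata, and so throws away 9 to 12 points of power. The document does not support that.

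- **Silence is not exclusion.** The article names a model class and lists no terms. It points to a pre-specified plan, where a covariate list would normally sit. The absence of the list is not an error in the article.
- **The mixed model may already do the job.** A repeated-measures model that includes the pre-treatment reading uses baseline. With a common baseline mean it is about as efficient as ANCOVA.
- **The named change-score method is not named for sick leave.** Mixed ANOVA is written for depression and anxiety only, where power is above 99% in any case.
- **The sample-size sentence may only fix the time points.** It sits in a sizing section and need not define an estimator.
- **The size rests on borrowed figures.** Rho is not documented, and the 0.15 and 0.4 describe dichotomous full return to work. Everyone is on sick leave at entry (Eligibility criteria), so that outcome has no baseline variation of its own. Only degree of sick leave can serve as covariate, and the +11.9 is an approximation.
- **Validity is not at stake.** Under randomisation the unadjusted comparison remains unbiased, and standard errors that are too large err on the cautious side.

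All of this stands, and it limits the point to one of precision. It does not remove the fact that the article describes the sick-leave comparison in two ways that need not give the same estimator, or that it names for the symptom scales a method whose usual group-by-time test is less precise than an available alternative.

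**Conclusion.** The point holds as a recommendation to improve precision, not as a demonstrated error. Neither the end-status comparison, the mixed model nor the mixed ANOVA is described with the screening value, gender or degree of sick leave as a term. If the first or last is carried out literally, or the mixed model is read through an unconstrained group-by-time test, it is less precise than a baseline-adjusted comparison for any rho between 0 and 1.

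The direction is general; the size is illustrative. The 9 to 12 points for sick leave require rho = 0.5 and an effect taken from full return to work. Over rho from 0.3 to 0.7 the loss is about 3 to 24 points against post-only and 2 to 19 against change score. It is about zero if the mixed model constrains the baseline means. For BDI-II and BAI only interval width is affected. No separate gain from including gender was calculated, because the document gives no figure for it.

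**What to change.** State one model for each co-primary (sick leave, BDI-II, BAI), in place of the end-status comparison and the mixed ANOVA group-by-time test. Either of these will do:

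- an ANCOVA of the end-of-treatment or end-of-wait value; or
- a linear mixed model with the baseline means constrained equal across arms.

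Both should have treatment arm, the screening (pre-randomisation) value of the outcome, gender and the randomisation category of degree of sick leave as fixed effects; in the constrained model the screening value enters as the baseline response. For registry sick leave, use the percentage before randomisation as baseline. If full return to work is also reported, adjust it for gender and degree of sick leave and give a standardised risk difference. If the unshown analysis plan already specifies such a model, it is enough to align the article's descriptions with it.

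The cost is wording and a few degrees of freedom out of 240 patients. The covariates are already collected, and nothing changes for patients or the site. Patients without a screening questionnaire can be kept through the constrained-baseline model or by simple imputation of the baseline value.
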